## 2.4. Stress

The effect of stress on a medical team during emergency management of patients must be considered, in that it compromises the security of patients (Gaba 2002). Stress covers all the biologic, electro-physiological and psychological disturbances that may be provoked by an aggression of some kind on the body. Stress provokes an emotional response - in particular, acute anxiety - as well as an alteration of cognitive processes (Kirschbaum 1996, Wolf 2003). The aeronautical industry has long ago admitted to the effects of stress on performance, with risks of decreased performance and human error (Kohn 2000, Loewenthal 2000). Performance losses were also reported in military and sports domains (Driskell 1991, Anshel 2002, Wallenius 2004). Stress decreases recognition of errors, by loss of continuous attention. It increases unsuitable answers during critical management (Sexton 2000). On the other hand, recognizing errors and factors of stress, associated to simulation-based training, improves aeronautical team performance and thereby increases passenger security (Sexton 2000).

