Stress has an important psychological effect. Post-traumatic stress state (PTSS) is a frequent pathology in clinical psychiatry, and in persons having undergone one (or more) traumatic event(s) during their lifetime (Yao 2003). One of the scales for evaluating the impact of post-traumatic stress one month later is the Post-traumatic Check List Scale (PCLS), which allows for a reliable approach of PTSS by auto-evaluation (Weathers 1993). There are other validated stress evaluation scales in English, translated and validated in French, such as the IES-R - Impact of Events Scale-Revised, very widely used by and recognized at an international level (Brunet 2003). The latter was created by Weiss and Marmar in 1996, based on Horowitz's Impact of Event Scale (Horowitz 1979), which was translated and validated in French by Brunet in 2003 (Laurent 2007). IES-R measures the presence of traumatic stress connected to recent, traumatizing events. The initial version of Horowitz's scale consisted of two axes: avoidance and repetition behaviour associated to traumatic symptomatology. In 1996, Weiss and Marmar added a third dimension: neurovegetative hyperactivity. Twenty two items thus evaluate the intensity of each symptom, using a Likert type scale ranging from "extremely" to "not at all" (Laurent 2007). The IES-R scale was validated by using numerous accident or aggression victims. It differentiates well subjects in a state of acute stress from presenting post-traumatic stress (Brunet 2003). A score of 22 would be indicative of an acute stress whereas a score of 36 would suggest the presence of PTSS, without, however, providing any diagnosis (Brunet 2003).

Professionals subjected to acute stress causes them to implement various stress management strategies (Anshel 2002). It was demonstrated that bad stress management has negative effects, notably in performance (Hassan 2006). It was recently reported in simulation studies, that the management of surgeons' stress was independent from any professional experience (Wetzel 2010). This particular team used an interview method of those involved, following simulation, so as to determine which of 6 predefined stress management strategies were applied.

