### **2.6.2. Risks**

#### 2.6.2.1. Individual risks

##### 2.6.2.1.1. Risks and physical constraints

Risks related to the participation are those of the discomfort caused by the bearing of a Holter during 24 hours, and the sampling of three salivary samples.

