#### 2.6.2.3. Expected individual and general adverse effects

None.

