### **2.6.3. Benefit / risk ratio**

This study offers a very positive benefit / risks ratio.

**2.7. Statement as to protocol observance, good clinical practices and current legal and statutory measures involved in the framework of this protocol**

The sponsor and the investigator also commit themselves to that this study will proceed:

- According to the protocol,
- According to France's best clinical practices guidelines and recommendations,
- According to current legal and statutory measures in France.

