##### **Psychological stress:**

will be assessed using 4 self-assessments:

- **Self-assessment** using STAI - *State-Trait Anxiety Inventory* (Spielberger 1983) just before and right after the simulation session, as well as following debriefing.
- Using **SOM self-rating scale** (Olpin 2010). For each self-assessment, participants will be placed in an isolated room so as not to be disturbed.
- **Early post-trauma stress disorder** will be determined on the 7th day following simulation, using IES-R - *Impact of Event Scale-Revised* (Brunet 2003), which will be emailed at that time to each participant.
- **Late post-trauma stress disorder** will be determined one month following simulation, using with PCLS - *Post-traumatic Check-List Scale* (Weathers 1993), which will be emailed at that time to each participant.

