#### **4.3.3.Stress**

Stress will be that which is connected to the very scenarios (hypoxia, haemodynamic decompensation, onset of convulsions), but also to an environment inducing a stressful atmosphere (monitor beeps and alarms), including the untimely entry of simulating parents into the emergency room, if this latter case has been foreseen in the scenario.

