- EIS-R is a self-assessment questionnaire, used for estimating early post-traumatic stress, 7 days following a trauma (in our case, "trauma" corresponds to the simulation session). This questionnaire will be sent out to the participants by e-mail at this time. Answers will be obtained by email return, and collected by a clinical research assistant.
- PCLS is a self-assessment questionnaire, used for estimating late post-traumatic stress, 28 days following a trauma (in our case, "trauma" corresponds to the simulation session). This questionnaire will be sent out to the participants by e-mail at this time. Answers will be obtained by email return, and collected by a clinical research assistant.

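### The risk section names no psychological risk although the study induces stress and measures post-traumatic stress after every session, and no investigator is required to see an IES-R or PCLS score before the participant's next session

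*Protocol*

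**What the plan says.** **Stress is intended and measured.** Protocol 4.3.3 attributes stress to the scenarios and to "an environment inducing a stressful atmosphere". Section 2.4 states: "Stress provokes an emotional response - in particular, acute anxiety". Section 4.1 places early and late post-traumatic stress among the primary outcome measures; the early form "will be determined on the 7th day following simulation, using IES-R", and the PCLS follows at one month (28 days in 7.3.2). Section 4.4.1 repeats the whole schedule at every session in both groups.

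**Risks.** Section 2.6.2.1.1 gives the risks of participation as "the discomfort caused by the bearing of a Holter during 24 hours, and the sampling of three salivary samples". Under the heading "Expected individual and general adverse effects" (2.6.2.3) the entry is simply none. Section 2.6.3 then concludes: "This study offers a very positive benefit / risks ratio".

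**Handling of the forms.** In 7.3.2 both questionnaires go out by e-mail. Of each it says: "Answers will be obtained by email return, and collected by a clinical research assistant". Section 2.4 gives reference levels for the IES-R: "A score of 22 would be indicative of an acute stress whereas a score of 36 would suggest the presence of PTSS". The same sentence adds that this is not a diagnosis. No action is tied to either level, and no level is given for the PCLS.

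**The concern.** The risk section makes a positive statement that does not fit the study's own premise. A protocol that sets out to provoke stress, says that stress brings acute anxiety, and screens for post-traumatic stress after each exposure has treated a psychological reaction as possible enough to measure. The benefit/risk conclusion in 2.6.3 therefore rests on a list that leaves out the kind of reaction under study.

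The second part is practical. Followed as written, a participant can return an IES-R total of 36 or more and go into the next session without anyone being required to review that score. The information would already be in the study's hands. What is at stake is participant protection and the soundness of the benefit/risk statement. No estimate, error rate or power figure depends on it.

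**Working it through.** **Inputs (protocol).** 12 teams of 4, six teams per group; 9 sessions in group 1 and 3 in group 2 (4.4.2, 4.5.1.2); sessions every 6 weeks or every 6 months (4.3.7); IES-R at day 7 and PCLS at day 28 (7.3.2).

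**The plan's own count.** 6 × 4 × 9 = 216 and 6 × 4 × 3 = 72; 216 + 72 = 288 participant-sessions, as in 4.4.2.3.

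**Sessions that follow an earlier one.**
- Group 1: 24 × (9 − 1) = 192.
- Group 2: 24 × (3 − 1) = 48.
- Total: 192 + 48 = 240 of 288, or 60 of 72 team sessions.
- Returns of each form with no later session: 288 − 240 = 48.

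**Time from sending a form to the next session.**
- Group 1 (42 days): 42 − 7 = 35 days for the IES-R; 42 − 28 = 14 days for the PCLS.
- Group 2 (6 months taken as 182 days): 182 − 7 = 175 days; 182 − 28 = 154 days.

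These gaps run from sending. 7.3.2 sets no deadline for return, so the time available after receipt may be shorter, most tightly for the PCLS in group 1.

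**Workload.** 288 × 2 = 576 forms. At an assumed 2 to 5 minutes each: 576 × 2 / 60 = 19.2 hours; 576 × 5 / 60 = 48 hours.

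**Does any existing safeguard put the score before an investigator in time?**
- Entry screening for relevant medical or psychiatric history (5.2): applies once, before any session.
- Debriefing (4.3.6): takes place on the session day, before either form exists.
- Adverse event recording and evaluation (8.1, 8.2) and follow-up to resolution (8.4): recurs through the study, but does not refer to IES-R or PCLS.
- Interruption of participation (4.7.1): gives the power to act, not the score.
- Investigator's signature on the CRF (4.8): falls at the end of data collection.
- Progressive entry, with investigators assisting electronic capture (13.1, 13.2): makes sight of a score possible, but does not require it before the next session.

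None of them closes the gap.

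**The case against.** The best case against is that symptoms, as opposed to scores, are already covered. The investigator must evaluate adverse events at each session, any unfavourable medical occurrence counts (8.3.1), participation can be interrupted in the participant's interest, and people with relevant psychiatric history are not enrolled. Participants are emergency-care professionals and residents in mannequin training. Measuring a construct is not forecasting harm, and routing of scores might sit in a data-handling procedure that is not shown. Listing a reaction as expected could also weaken expedited reporting of serious cases under 8.3.3.3.

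Much of this stands. Overt symptoms would probably be picked up, and a reader who inferred that the study has no safety oversight would be wrong. The reporting point is fair too: expectedness is judged against the investigator's brochure (8.3.1, 8.3.3.1), which is not shown, so the fix should say expressly that serious reactions stay under expedited reporting.

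Two further inferences are tempting and unsupported. The word trauma in 7.3.2 only anchors the questionnaires to an index event; it does not say that sessions traumatise. And the absence of a psychological risk from 2.6.2 does not show that participants go unwarned: 12.3 says the information form covers possible risks, and that form is not available here.

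What does not stand is the argument that this is only missing detail. Section 2.6.2 makes a definite statement about risk, and 7.3.2 names a recipient for the forms without carrying the result any further.

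**Conclusion.** The point holds in two limited parts. The risk section omits psychological stress reactions although the study induces stress and measures post-traumatic stress repeatedly. And no provision in the protocol requires an investigator to see an IES-R or PCLS score before the participant's next session.

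The size is 240 re-exposures among 288 participant-sessions. It might be read as a number at risk of harm, but the protocol gives no rate of high scores and none is assumed. Likewise 22 and 36 are not diagnostic cut-offs. They come from background text on a scale validated in accident or aggression victims, and nothing in the protocol supports them for simulation trainees. They can serve only as signals.

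The counts are exact under the planned schedule; the group 2 gaps rest on taking 6 months as 182 days. This is a cheap improvement in participant safety and in the consistency of the protocol. It is not a statistical error.

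**What to change.** 1. **Section 2.6.2.** Name psychological stress reactions as a foreseeable risk and state that serious ones remain under expedited reporting in 8.3.3.3. Check that the information sheet agrees. In the same edit, correct three saliva samples to four per session, as in 4.4.2.6.
2. **Section 7.3.2.** Have the research assistant total each form on receipt. IES-R totals of 36 or more (optionally 22 or more), and PCLS totals above a level that the sponsor sets, go in confidence to one designated investigator. Where possible this person should not rate that team and should have no line-management role over the participant. Review takes place before the next session, or promptly after the last one. The total is a non-diagnostic signal; the investigator decides on interruption under 4.7.1 and on adverse event recording, with no automatic stop.

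**Costs.** A few sentences of text, and about 19 to 48 hours of totalling under the 2 to 5 minute assumption, by staff who already receive the forms. Nurses and drivers come from the sponsor's hospital, so reviewing investigators may be colleagues; participants who know that scores are reviewed may under-report, hence the confidentiality terms. Acting on a score may affect later stress measurements, and both forms are primary-outcome measures. Excluding one member removes a whole team of the 12 and requires a replacement (5.5.1.1), which is the reason for leaving the decision to judgement.

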## 8. ASSESSMENT OF SAFETY

### 8.1. Evaluation parameters concerning safety

Clinical tolerance during the research study will be objectivised by analysis of all adverse and/or intercurrent events that may arising during the research study, and which should systematically be reported within the observation notebook.

### 8.2. Methods and schedule for collection, quantification and analysis of safety evaluation parameters

Adverse events will be evaluated at each and every session during the entire study phase.

It will be asked of every investigator to note: the severity of the event, the type of event, its intensity, its relation with the simulation session (improbable, likely, not assessable), the date of onset, its duration, and treatment initiated.

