#### 4.3.7. Simulation session repetition

The frequency of repeated simulation sessions will be one of the varying parameters, and will define distribution into one of two randomized groups, necessary for providing answers to secondary objectives. Repetition will take place either every 6 weeks i.e. 9 / year (group 1), or every 6 months i.e. 3 / year (group 2).

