### 4.4. Study schedule

#### 4.4.1. Time schedule of measurements

Time schedule of measurements

| Variables         |                    | day prior | Before Sim | Sim | Post Sim | Debrief | Post debrief | H+2 | 1 week | 1 month |
|-------------------|--------------------|-----------|------------|-----|----------|---------|--------------|-----|--------|---------|
| PERFORMANCE       | Global Performance |           |            | X   |          |         |              |     |        |         |
|                   | IO access          |           |            | X   |          |         |              |     |        |         |
|                   | Leadership (BAT)   |           |            | X   |          |         |              |     |        |         |
|                   | Teamwork (CTS)     |           |            | X   |          |         |              |     |        |         |
| STRESS PARAMETERS | Salivary cortisol  | X         | X          |     | X        |         | X            |     |        |         |
|                   | Holter parameters  | X         | X          | X   | X        | X       | X            | X   |        |         |
|                   | BP HR              | X         | X          |     | X        |         | X            |     |        |         |
|                   | SOM                |           | X          | X   |          |         |              |     |        |         |
|                   | STAI scale         | X         | X          |     | X        |         | X            |     |        |         |
|                   | EIS-R scale        |           |            |     |          |         |              |     | X      |         |
|                   | PCLS scale         |           |            |     |          |         |              |     |        | X       |

This plan will be repeated on each and every simulation session, that either every 6 weeks (as concerns the teams of group 1) or every 6 months (as concerns the teams of group 2).

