#### **4.6. Study duration**

Total duration of the study is estimated at **24 months**

Total duration of participation in the study for each participant: **12 months**

Starting from very first inclusion, the sponsor must immediately, and without any delay, inform the proper authorities and France's Protection Committee of Human Subjects (CPP - "Comité de Protection des Personnes) as to the effective date of study onset (effective date of study onset = date of signature of consent made by the first participant included in the study).

The date of study end will be transmitted by the sponsor to the France's National Agency of Medication and Health Product Security ("ANSM - Agence Nationale de Sécurité du Médicament et des produits de santé") and to the CPP within a period of 90 days following that date.

The date of study end corresponds to the participation end term of the last participant included in the study, or if need be, **to the end term as defined in the protocol.**

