#### **4.8. Identification of all data to be collected directly in observation manuals and to be considered as data sources**

A CRF paper will be provided to the investigators, in which clinical data will be directly noted by the included participants.

Data collected in the CRF will so be able to be considered as data sources. The investigator should date and sign this copy at the end of data collection.

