#### 8.3.2.2. Reporting of non-severe adverse events

All the other Adverse events will be reported on the form "Adverse event" (« événement indésirable ») included in the observation notebook, while noting the following: date of onset, description, intensity, duration, mode of resolution, aetiology, imputability and decisions taken.

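### Adverse-event enquiry is scheduled only at the sessions, so its delay differs by arm and none follows the last session; group 2's last questionnaires also fall after the stated 12 months of participation

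*Protocol*

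**What the plan says.** Protocol 8.1 rests tolerance on a full record: "Clinical tolerance during the research study will be objectivised by analysis of all adverse and/or intercurrent events". Section 8.2, whose title covers the schedule for collection, then states: "Adverse events will be evaluated at each and every session during the entire study phase". It names no other time point, and the measurement table in 4.4.1 has no adverse-event row.

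Session frequency is what is randomised (4.3.7, 4.5.1.2): "either every 6 weeks i.e. 9 / year (group 1), or every 6 months", the latter being group 2 with three sessions.

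Other provisions bear on the point:
- Serious events, including any that the investigator finds alarming (8.3.1), are reported from consent until 4 weeks after follow-up ends (8.3.2.1.4).
- For non-serious events, 8.3.2.2 says "All the other Adverse events will be reported on the form" in the observation notebook, without a time of enquiry. On the notebook, 4.8 says: "A CRF paper will be provided to the investigators, in which clinical data will be directly noted by the included participants".
- Events already known are followed to resolution (8.4).
- IES-R at day 7 and PCLS at day 28 are e-mailed as stress measures. PCLS is "used for estimating late post-traumatic stress, 28 days following a trauma" (7.3.2). On the whole measurement plan, 4.4.1 says: "This plan will be repeated on each and every simulation session".

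Section 4.6 gives the "Total duration of participation in the study for each participant" as 12 months.

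**The concern.** When adverse events are asked about depends on the allocated programme. The protocol itself looks for delayed reactions at days 7 and 28 after a session, but the next scheduled adverse-event evaluation comes much later in group 2 than in group 1, and after the last session it does not come at all. Section 8.2 wants onset date, duration, intensity and relation to the session. For a mild, short-lived event these are harder to establish after half a year than after six weeks. At stake is the completeness and comparability of the descriptive record of non-serious events.

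The second matter is one of dates: a 12-month participation period does not contain the questionnaires that the protocol schedules after group 2's third session.

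**Working it through.** **Inputs.** 6 teams of 4 per group, so 24 participants per group; 9 and 3 sessions (4.4.2); intervals of 6 weeks and 6 months (4.3.7); questionnaires at days 7 and 28 (7.3.2); participation of 12 months (4.6). Day 0 is taken as the first session, since signed consent is obtained the day before it (5.4). Six months is taken as 182 days and 12 months as about 365.

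**The plan's own counts.** 24 × 9 = 216 and 24 × 3 = 72, total 288 individual sessions. These match 4.4.2.3.

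**Sessions with and without a later scheduled evaluation.**

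| | Group 1 | Group 2 |
|---|---|---|
| With | 24 × 8 = 192; 192/216 = 89% | 24 × 2 = 48; 48/72 = 67% |
| Without (last session) | 24/216 = 11% | 24/72 = 33% |
| Interval between evaluations | 42 days | about 182 days |
| Day 28 to next evaluation, where there is one | 42 − 28 = 14 days | 182 − 28 = 154 days |

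**Effect on a per-session event rate, if one were tabulated.** Assume equal true risk per session, look-back with perfect recall at the next session, and session-day events always recorded. Let d be the share of events that arise after the session day, and s the share of those following the last session that is reported unprompted. With u = d(1 − s), the recorded share is 1 − u/9 in group 1 and 1 − u/3 in group 2. The apparent ratio of group 1 to group 2 is (1 − u/9)/(1 − u/3):
- d = 1, s = 0: 0.889/0.667 = 1.33
- d = 1, s = 0.5, or d = 0.5, s = 0: 0.944/0.833 = 1.13
- d = 0.25, s = 0: 0.972/0.917 = 1.06
- s = 1, any d: 1.00

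The documents give neither d nor s. If 8.2 means same-day events only, the ratio is also 1.00, but then neither group has a scheduled adverse-event enquiry covering days 7 to 28.

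**Effect on a per-participant view over 12 months.** Group 1's last evaluation is at day 8 × 42 = 336, and group 2's at about day 365. With look-back, evaluations cover 336/365 = 92% of group 1's 12 months and all of group 2's. On this denominator the uncovered stretch lies in group 1.

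**Questionnaires against the 12 months.** Group 1: 336 + 28 = day 364, so 0 of 24 × 9 × 2 = 432 fall outside. Group 2: third session at about day 365, then day 365 + 7 = 372 and 365 + 28 = 393 (about 12.9 months). So 24 × 2 = 48 of 24 × 3 × 2 = 144 fall after month 12.

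**The case against.** The strongest reply is that no planned analysis is harmed. Section 9 contains no between-group comparison of adverse events, and how they are tabulated may be left to an analysis plan that is not shown. The study involves healthy volunteers. The stated individual risks are discomfort from the Holter and saliva sampling (2.6.2.1.1), which arise around the session, and no adverse effects are expected (2.6.2.3). Section 8.1 requires systematic recording of all events, 4.8 has participants entering data themselves, and serious events are covered beyond the end of follow-up. The most plausible delayed harm, post-traumatic stress, is measured at the same delays after every session in both groups.

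Most of this stands and keeps the point small. What it leaves untouched is that these provisions say where a known event is recorded and for how long serious ones are reported. None adds a scheduled enquiry about non-serious events, and IES-R and PCLS ask only about their own listed symptoms.

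A reader might infer that a third of group 2's events go unrecorded, or that the three-session programme will look better tolerated than it is. The documents support neither. The 33% counts sessions, and it concerns only events arising after the last one, that is, after month 12. The 1.33 ratio needs every event to be delayed and none after the last session to be volunteered. The direction also changes with the denominator, as the per-participant calculation shows.

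On 4.6, one may say that 12 months is a rounded figure and that 4.4.1 plainly schedules the later questionnaires. That is a fair account of the intention, but the stated period should agree with the schedule, particularly as 4.6 defines the end of the study by the last participant's end of participation.

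**Conclusion.** The point holds as a minor one. Section 8.2 ties the only scheduled enquiry about non-serious adverse events to the sessions, so its delay differs by arm (about 6 weeks against about 6 months) and it is absent after the last session (24 of 216 and 24 of 72 individual sessions). The counts rest on the protocol's nominal schedule. Any bias in event rates is of unknown size and uncertain direction: under the stated assumptions the per-session ratio lies between 1.00 and 1.33, with the upper end a worst case. No conclusion about the trial's planned comparisons follows, and the stress comparison in 9.1.5 is not affected by the adverse-event point.

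The mismatch in 4.6 does not depend on how 8.2 is read. On nominal dates, 48 of group 2's 144 questionnaires, and none of group 1's 432, fall after the stated participation period.

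**What to change.** Two sentences.
- In 8.2: include one question on adverse events since the session in the day-28 PCLS e-mail after every session, including the last, in both groups.
- In 4.6: end participation at day 28 after the last session, which is about 13 months in group 2.

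Sessions with no later scheduled enquiry then fall from 11% and 33% to 0% in both groups, and the first enquiry after any session comes within 4 weeks. This equalises enquiry per session but not the number of prompts per participant (9 added in group 1, 3 in group 2). Group 2 events arising between day 28 and the next session still wait for that session.

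The cost is one question in an e-mail already planned for each of the 288 individual sessions, and handling of the replies by the research assistant who already collects them. No visit, sample or test is added. Section 9.1.5 and the role of IES-R and PCLS as stress measures can stay as they are.
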